**Custodiol Versus Blood Cardioplegia in Pediatric Cardiac Surgery**

**Research Proposal IRB # 2016-08**

**Study Overview**

**Brief Summary:**

Cardioplegic arrest is an essential part of cardiac surgery which aims to allow myocardial preservation and minimize myocardial swelling, while providing a motionless and bloodless field, Blood cardioplegia has proven its efficacy for several decades and surgeons are still preferring to use it for myocardial protection of pediatric cardiac surgery, although it is thought to be more time consuming since it is given with interrupted doses, Even when advancement has come along the field of myocardial protection and cardioplegia solutions with the introduction of Bretschneider Histidine-Tryptophan-Ketoglutarate solution , custodiol ,in 1970 ,which is given as single dose and believed to be convenient, simple to deliver , and less time consuming .Many Surgeons haven't change their practice possibly due to paucity of studies comparing cardioplegia solutions in pediatric cardiac surgery and conflicting reports regarding the superiority of different cardioplegia solution. The investigators aim to provide evidence that will help pediatric cardiac surgeons to choose the optimal solution for their practice.

**literature review:** After an extensive literature review the investigators found only one randomized trial by Elmorsy et al, which concluded that A single dose of an HTK cardioplegic solution provides better myocardial and cerebral protection than repeated doses of oxygenated blood cardioplegia during pediatric congenital cardiac surgery.

On the other hand, there was another retrospective report by bojan et al, found that the use of Custodiol cardioplegia in neonates undergoing ASO was associated with a larger troponin release when compared with warm blood cardioplegia, p <0.001 suggesting poor myocardial protection.

Koruon et al, done a tissue level comparison between htk and conventional crystalloid cardioplegia and their statistical analysis revealed no significant difference between the two groups regarding the clinical variables, apoptotic indices and proliferation indices.

Liu j et al, did a retrospective study comparing custodiol to St. Thomas crystalloid cardioplegia which concluded That HTK group had shorter cross-clamping time and more frequent spontaneous defibrillation than St. Thomas group.

Also, an animal study by Chen Y et al, on piglets that were randomized to either a single dose of HTK or multidose cold blood cardioplegia. No significant differences were noted in the myocardial lactate content, ATP content, and histopathological score between both groups.

Finally, a retrospective report by E Qulisy et al concluded that Custodiol cardioplegia is associated with less myocardial protection and higher adverse outcomes compared to blood cardioplegia in pediatric age group undergoing cardiac surgery.

**Detailed Description:**

**Hypothesis**:

Custodial is not inferior to blood cardioplegia in myocardial protection in pediatric cardiac surgery.

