**Randomization:**

Computer generated randomization into two groups based on cardioplegia solution. if randomized to blood patient will receive blood cardioplegia, delivered by microplegia delivery system by adding potassium to the blood (K= 35 ml eq/L). The initial dose will be 35ml/ kg, and subsequent doses 20-15 ml/kg given every 20 minutes at a Temperature of 10 - 15 C, while maintaining a perfusion pressure of 100-125 mmg. if randomized to custodial patient will receive single dose of HT custodiol cardioplegia. at temperature of 4-8°C and will be perfused for 6-8 minutes. Dose will start from 400 up to 1000 ml according to the child's body weight. Perfusion pressure will be kept at 70 - 80 mmHg until the heart is arrested.

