**Blinding:**

Surgeons will know the type of cardioplegia in the OR while another assessor will be blinded.

Sample size calculated with an online calculator based on α _error of 0.05 and β _error of0.2 to detect an absolute risk difference of 15% in composite end point between the twogroups yielded 137 in each arm, the results will be presented as mean (SD), median

(interquartile range), or proportion. Using relative risk and log rank for statistical analysis. A P value of less than 0.05 will be considered statistically significant. Statistical analyses will be carried out using the SPSS.

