**Outcomes:**

Primary end point will be composite of mortality (30d); ICU stay more than 5daysand post-operative arrhythmia requiring intervention (48h). Secondary end point length of hospital stays(days), length of mechanical ventilation (days), myocardial biomarkers (troponin, CKMB), ventricular function by echo, CMO, inotropic score sample size calculated with an online calculator basis of an error of 0.05 and a B error of 0.2 to detect an absolute difference of 15% in composite end point between the two gps yielded 137 in each arm, the results will be presented as mean (SD), median (interquartile (range), or proportion. Using relative risk for statistical analysis and log rank. A P value of less than 0.05 will be considered statistically significant. Statistical analyses will be carried out using the SPSS

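### The only stated hypothesis is non-inferiority, but the trial is sized and judged as a test of difference at P<0.05, with no margin and no confidence-limit rule

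*Protocol*

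**What the plan says.** The Hypothesis section of the Protocol holds one sentence: "Custodial is not inferior to blood cardioplegia in myocardial protection in pediatric cardiac surgery".

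The sample-size text sits under Blinding. It uses "α _error of 0.05 and β _error of0.2" and aims "to detect an absolute risk difference of 15% in composite end point between the twogroups yielded 137 in each arm". The decision rule follows: "A P value of less than 0.05 will be considered statistically significant". The Outcomes section repeats the basis ("to detect an absolute difference of 15% in composite end point"), the 137 per arm and the same significance rule. Both sections name relative risk and log rank as the methods.

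Study design says only that the trial is randomized and controlled. Nowhere does the Protocol state a non-inferiority margin, the sidedness of the test, a confidence bound to be compared with a margin, or a control event rate for the composite. Safety monitoring and interim results adds an interim analysis every six months.

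**The concern.** A test of difference tries to reject the claim that the two arms have equal risk. A non-inferiority test tries to reject the claim that Custodiol is worse by at least a stated margin. These are different null hypotheses. The Protocol states its hypothesis in the second form and provides sizing and a decision rule only for the first.

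P<0.05 would show that the arms differ. P>0.05 would show only that a difference was not demonstrated, which happens more often with fewer patients or fewer events. Neither result answers the stated question.

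The stakes are real on the Protocol's own account. Its literature review cites a retrospective report of larger troponin release with Custodiol and another of more adverse outcomes. The composite includes 30-day mortality, and the stated aim is to guide surgeons' choice of solution.

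**Working it through.** **Inputs.** From the Protocol: 137 per arm, a 15-point absolute difference, alpha 0.05, beta 0.2. Assumed because not stated: a two-sided test, and a control rate p between 10% and 35%.

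**1. The plan's own figure.** For a two-sided difference test with p1 = 0.20, p2 = 0.35 and mean rate 0.275:

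n = [1.96·√(2·0.275·0.725) + 0.8416·√(0.20·0.80 + 0.35·0.65)]² / 0.15² = (1.2377 + 0.5239)² / 0.0225 = 137.9, so 138 per arm.

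Lower-arm rates of 19% and 21% give 135 and 141. So 137 fits an ordinary difference design with a control rate near 20%. Because no rate is stated, the figure cannot be reproduced uniquely. Some non-inferiority inputs with a 15-point margin also come near it: one-sided 0.025 at a 25% rate gives 131, and one-sided 0.05 at a 50% rate gives 138. The number alone therefore does not settle the design. The wording about detecting a difference and the P<0.05 rule do.

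**2. How often P>0.05 occurs when Custodiol is truly worse by d.** With SE0 = √(2·p̄(1−p̄)/137), where p̄ is the mean of the two rates, and SE1 = √([p1(1−p1) + p2(1−p2)]/137):

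P(P>0.05) = 1 − Φ[(d − 1.96·SE0)/SE1].

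- 20% vs 30%: SE0 = 0.05232, SE1 = 0.05197. (0.10 − 0.10255)/0.05197 = −0.049, giving 52%.
- 20% vs 35%: SE0 = 0.05395, SE1 = 0.05318. (0.15 − 0.10574)/0.05318 = 0.832, giving 20%.

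| Control rate | Truly +10 points | Truly +15 points |
|---|---|---|
| 10% | 36% | 9% |
| 20% | 52% | 20% |
| 30% | 59% | 27% |
| 35% | 61% | 29% |

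For comparison, a single non-inferiority test at one-sided 0.025 with a 15-point margin would pass about 2.5% of the time when the true excess is 15 points.

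**3. A worked result.** Take 27/137 on blood (19.7%) and 40/137 on Custodiol (29.2%). The difference is +9.5 points. The pooled test gives z = 0.0949/0.0519 = 1.83, P = 0.068. The unpooled 95% CI is 9.5 ± 1.96·5.16, that is −0.6 to +19.6 points. Test and interval agree that the result is not significant, yet the upper limit lies beyond 15 points.

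**4. Non-inferiority power at 137 per arm.** With equal true rates and a single analysis at one-sided 0.025, SE = √(2p(1−p)/137) and power = Φ(margin/SE − 1.96). At p = 0.20, SE = 0.0483: Φ(3.104 − 1.96) = 87% for 15 points and Φ(2.069 − 1.96) = 54% for 10 points. The n per arm for 80% power is 2p(1−p)(1.96 + 0.8416)²/margin².

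| Control rate | Power, 15-point margin | n for 80% | Power, 10-point margin | n for 80% |
|---|---|---|---|---|
| 20% | 87% | 112 | 54% | 252 |
| 25% | 82% | 131 | 48% | 295 |
| 30% | 77% | 147 | 44% | 330 |
| 35% | 74% | 159 | 41% | 358 |

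**The case against.** The best defence is that the hypothesis is one informal sentence. The study design, the sizing, the test and the aim of helping surgeons choose between solutions all fit an ordinary two-group comparison. On that reading only the hypothesis sentence needs rewording. This has force, and it is the cheaper of the two repairs, but it concedes that the sections disagree.

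A second defence is that a SAP may supply a margin. It does not remove the problem. The Protocol itself fixes the hypothesis, the basis for N and the significance rule, and these conflict with one another.

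Three stronger readings are tempting and are not supported:

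- A reader might infer that the investigators will report P>0.05 as proof of non-inferiority. The Protocol does not say so. It says only how significance is judged and gives no other route to its hypothesis.
- A reader might take the 15 points as an implied margin. The text presents it as a difference to detect. At a 20% control rate, a margin of that size would tolerate a rate approaching 35% on a composite that includes death, so it would need its own justification.
- A reader might conclude that 137 is miscalculated. With no control rate stated, that cannot be shown, and 137 is close to what 20% vs 35% requires.

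**Conclusion.** The point stands as a contradiction within the Protocol: a non-inferiority hypothesis alongside difference-based sizing and a P<0.05 rule, with no margin. It should be resolved, because the primary analysis as described cannot establish the only hypothesis stated.

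Its size depends on a control rate that the Protocol does not give. Over an assumed 10% to 35%, a non-significant result would accompany a true 10-point excess on Custodiol in about a third to three fifths of trials, and a true 15-point excess in roughly one trial in eleven to two in seven. These figures assume a two-sided z test, a single analysis and complete data on 137 per arm. They measure how little a non-significant result would show; they do not predict how the investigators would report one.

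**What to change.** Make Hypothesis, Blinding and Outcomes agree by one of two routes.

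**(a) Test of difference.** Restate the hypothesis as a two-sided comparison of the composite, which is what the other two sections describe. Add that P>0.05 will not be taken as evidence of non-inferiority. Cost: wording only; N is unchanged.

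**(b) Non-inferiority.** State a margin on the composite and justify it clinically before any outcome comparison is made. Conclude non-inferiority only if the upper confidence limit for Custodiol versus blood lies below that margin. Set the confidence level to allow for the six-monthly looks in Safety monitoring and interim results. Use 15 points as the margin only if the sponsor can defend it. State the control rate and restate the power at 137 per arm. Cost: that power may fall below 80%. In the single-analysis table above, 137 per arm reaches 80% only for a 15-point margin at control rates of 20% and 25%. At 30% or above, or with a 10-point margin, the sponsor would have to accept and state lower power or increase N.

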**Methodology:**

**Study design:**

Randomized controlled trial

**Data collection**:

All demographic data, diagnosis, procedure (type. CPB time, cross-clamp time), surgeon and hospital course details.

**Inclusion criteria:**

- All pediatric patients (10 to 18y) referred to our hospital which will undergo open cardiac repair with cardiopulmonary bypass

**Exclusion criteria:**

- All emergency procedure (require immediate surgery)
- Cases that don't require use of cardioplegia.

**Randomization:**

Computer generated randomization into two groups based on cardioplegia solution. if randomized to blood patient will receive blood cardioplegia, delivered by microplegia delivery system by adding potassium to the blood (K= 35 ml eq/L). The initial dose will be 35ml/ kg, and subsequent doses 20-15 ml/kg given every 20 minutes at a Temperature of 10 - 15 C, while maintaining a perfusion pressure of 100-125 mmg. if randomized to custodial patient will receive single dose of HT custodiol cardioplegia. at temperature of 4-8°C and will be perfused for 6-8 minutes. Dose will start from 400 up to 1000 ml according to the child's body weight. Perfusion pressure will be kept at 70 - 80 mmHg until the heart is arrested.

**Blinding:**

Surgeons will know the type of cardioplegia in the OR while another assessor will be blinded.

Sample size calculated with an online calculator based on α _error of 0.05 and β _error of0.2 to detect an absolute risk difference of 15% in composite end point between the twogroups yielded 137 in each arm, the results will be presented as mean (SD), median

(interquartile range), or proportion. Using relative risk and log rank for statistical analysis. A P value of less than 0.05 will be considered statistically significant. Statistical analyses will be carried out using the SPSS.

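### The protocol's hypothesis is non-inferiority, but 137 per arm is sized to detect a 15-point difference with no event rate, sidedness or margin, so the 80% power is not shown to apply to the trial's own question

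*Protocol*

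**What the plan says.** Under Hypothesis (Detailed Description), the protocol states: "Custodial is not inferior to blood cardioplegia in myocardial protection in pediatric cardiac surgery". No margin is attached to it.

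The sample-size text, in the section headed Blinding, uses "α _error of 0.05 and β _error of0.2" and continues "to detect an absolute risk difference of 15% in composite end point between the twogroups yielded 137 in each arm". The same calculation appears again under Outcomes: "to detect an absolute difference of 15% in composite end point between the two gps yielded 137 in each arm". Both copies plan relative risk and log rank for the analysis, and the criterion is that "A P value of less than 0.05 will be considered statistically significant".

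The primary endpoint is a binary composite of 30-day death, ICU stay beyond 5 days, and arrhythmia needing intervention within 48 hours. The protocol gives no expected rate of this composite in either arm. It does not say whether alpha is one- or two-sided, and it makes no allowance for dropout.

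**The concern.** Two different questions are in play. Power to detect a difference is the chance of a significant result when the arms truly differ by 15 points. Power for non-inferiority is the chance of excluding a stated margin when the arms are about equal. The protocol poses the second question and gives a beta worded for the first. A non-significant P value on relative risk or log rank would not establish non-inferiority.

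In addition, the sample size for an absolute difference between two proportions depends on the base rate. Without that rate, 137 per arm and 80% power cannot be tied together from the document. What is at stake is whether a reader can rely on the stated power for the conclusion the trial wants to draw.

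**Working it through.** **Inputs from the protocol.** Alpha 0.05, power 0.80, absolute difference 0.15, 137 per arm, equal arms.

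**Assumptions, because the protocol gives no figure.** Event rates 10% to 57%; two-sided alpha for the difference test; one-sided 0.025 for non-inferiority unless stated otherwise; margins of 15 and 10 points; no dropout; no adjustment for the six-monthly interim analyses described under Safety monitoring and interim results.

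**1. Reproducing 137 as a difference test.** With p̄ = (p1 + p2)/2,

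n = [1.96·√(2p̄(1−p̄)) + 0.842·√(p1(1−p1) + p2(1−p2))]² / 0.15².

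At 20% versus 35%, p̄ = 0.275, so 2p̄(1−p̄) = 0.39875 and the second sum is 0.16 + 0.2275 = 0.3875. Then n = (1.2377 + 0.5239)² / 0.0225 = 137.9. At 19.5% versus 34.5% the rounded-up result is exactly 137. The stated number is therefore arithmetically sound for a rate near 20%.

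**2. Other readings that give the same number.**
- Difference test with continuity correction: about 16% versus 31%.
- Difference test at one-sided 0.05: about 42% versus 57%.
- Non-inferiority with a 15-point margin and equal true rates p, n = (z_α + z_β)²·2p(1−p)/0.15². At one-sided 0.025 and p = 27%: 7.849 × 0.3942 / 0.0225 = 137.5. At one-sided 0.05 and p = 50%: 6.183 × 0.5 / 0.0225 = 137.4.

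The number alone does not show which calculation was run.

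**3. Power of the two-sided difference test for 15 points, 137 per arm.** Power = Φ{[0.15·√137 − 1.96·√(2p̄(1−p̄))] / √(p1(1−p1) + p2(1−p2))}.

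| Rates | Power |
|---|---|
| 10% vs 25% | 90.9% |
| 15% vs 30% | 84.8% |
| 20% vs 35% | 79.7% |
| 25% vs 40% | 75.8% |
| 30% vs 45% | 73.0% |
| 40% vs 55% | 70.3% |
| 42.5% vs 57.5% (floor) | 70.2% |

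**4. Power for non-inferiority, 137 per arm, one-sided 0.025, equal true rates.** Power = Φ(margin/SE − 1.96), with SE = √(2p(1−p)/137). For example, at p = 20% SE = 0.0483. A 15-point margin gives Φ(3.104 − 1.96) = 87.4%, and a 10-point margin gives Φ(2.069 − 1.96) = 54.3%.

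| True rate, both arms | 15-point margin | 10-point margin |
|---|---|---|
| 10% | 98.5% | 78.8% |
| 20% | 87.4% | 54.3% |
| 30% | 77.3% | 43.9% |
| 50% | 70.0% | 38.0% |

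**5. What a 15-point margin would let through.** Take 20% on blood cardioplegia and a true 34.9% on Custodiol. Then SE = √((0.16 + 0.2272)/137) = 0.0532, and the chance of passing is Φ((0.15 − 0.149)/0.0532 − 1.96), about 2.6%. At a true 30% the chance is about 16%. To pass, the observed excess must be below about 5 points (0.15 − 1.96 × 0.05).

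**The case against.** The strongest reply is that 137 is not wrong. It reproduces under a standard formula, and it also fits a 15-point non-inferiority margin at 27% events, in which case 80% would be exactly the non-inferiority power. This stands, and it limits the point to what has not been shown. A reader might conclude that 80% cannot be the non-inferiority power, but the number does not establish that. The wording does favour a difference test: the text speaks of detecting a difference, sets no margin and judges by P<0.05.

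A second reply is that a statistical analysis plan may supply the missing assumptions. That would answer an omission. Here, however, the protocol itself fixes alpha, beta, effect size and sample size, twice, and attaches them to a question other than its hypothesis.

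Three stronger readings are tempting and unsupported:
- *The trial is underpowered.* Difference-test power exceeds 80% when the lower rate is below about 20%, and nothing in the protocol favours higher rates over lower ones. The 70% is a floor.
- *The trial has even odds or worse of showing non-inferiority.* With a 10-point margin, power is about 54% at a 20% rate and below 50% at 30%, but 79% at 10%. The protocol gives neither the rate nor that margin.
- *With a 15-point margin the trial would accept a true rate just under 35% against 20%.* The margin is what the confidence limit must exclude. Such a rate would pass only about 2.6% of the time.

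**Conclusion.** The point holds as a conflict between the hypothesis and the sample-size text, compounded by unstated assumptions. It is not an arithmetic error. The stated 80% is, as worded, the power of a difference test, and its link to non-inferiority is not shown. Depending on the missing inputs, power with 137 per arm is 70% to 91% for detecting 15 points over the rates examined. For non-inferiority it is 70% to 98.5% with a 15-point margin and 38% to 79% with a 10-point margin.

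These ranges rest on normal approximations, full follow-up, the assumed sidedness, equal true rates for non-inferiority, and no allowance for interim looks. The 20% rate and both margins are illustrations, not figures from the protocol. The matter should be corrected, because the primary conclusion rests on this paragraph.

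**What to change.** Make the hypothesis and the sample-size paragraph agree. Keep 137 per arm, write the paragraph once, and delete the copy under Outcomes.

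**If non-inferiority is the aim,** state:
- the assumed composite rate on blood cardioplegia, taken from the hospital's own records;
- a margin justified independently of the sample size, not chosen because it fits 137;
- the sided alpha;
- the power that 137 per arm then delivers.

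Judge non-inferiority by the confidence limit of the risk difference against that margin.

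**If the aim is to detect a difference,** reword the hypothesis accordingly, and give the sidedness and the power at the assumed rate.

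In either case, check the pooled event rate during the trial without splitting by arm, and restate the power if the rate differs from the assumption.

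The cost is one rewritten paragraph, a look at local records and a simple blinded check, with no extra patients. The downside is that the honestly stated power may be lower than 80%.

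### The named primary analysis uses no baseline covariates although case-mix data are already collected; the crude comparison is valid but gives up precision that a pre-specified adjusted relative risk would recover

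*Protocol*

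**What the plan says.** The analysis is named twice. The paragraph under Blinding that holds the sample size says "Using relative risk and log rank for statistical analysis", and the Outcomes section says "Using relative risk for statistical analysis and log rank". Neither place mentions a covariate, a regression model or a stratified test, and none appears elsewhere in the protocol.

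The primary endpoint (Outcomes) is a composite of death by 30 days, an ICU stay of more than five days, and arrhythmia needing intervention within 48 hours.

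The Inclusion criteria admit open repairs on bypass in general. The Exclusion criteria remove only emergencies and cases that need no cardioplegia. The case mix is therefore broad by design.

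The Data collection section lists "All demographic data, diagnosis, procedure (type. CPB time, cross-clamp time), surgeon and hospital course details". Age is not named, but it falls under demographic data. Procedure type stands in the same item as bypass and cross-clamp time.

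The Randomization section says "Computer generated randomization into two groups based on cardioplegia solution" and names no stratification factor.

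The sample size rests on "α _error of 0.05 and β _error of0.2", is set "to detect an absolute risk difference of 15% in composite end point between the twogroups", and "yielded 137 in each arm". No control event rate and no sidedness are stated.

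**The concern.** A relative risk and a log-rank test, named without further detail, are ordinarily read as crude comparisons of two groups. In a trial that mixes operations, the risk of a long ICU stay, an arrhythmia or death can be expected to differ between procedures. When such a factor is known before randomisation and recorded anyway, adjusting for it removes part of the outcome variation from the treatment comparison and narrows the confidence interval at the same sample size.

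Width matters here because the Hypothesis section frames the question as Custodiol being not inferior, and that conclusion is read from a confidence limit.

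There is also a trap in the data list. Bypass and cross-clamp time sit beside procedure type, so an analyst who later decides to adjust for procedure could pick them up too. Both arise after randomisation. The protocol's own summary says that blood cardioplegia, given in interrupted doses, is thought to take more time than a single-dose solution. Adjusting for these times could therefore remove part of the effect under study.

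**Working it through.** **Inputs from the protocol:** 137 per arm (274 in total), error rates 0.05 and 0.2, and a 15-point absolute difference.

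**Inputs assumed:** event rates, a two-sided test, and the share of outcome variance explained by baseline factors (R²).

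**Step 1. The plan's own figure.** The protocol's inputs alone do not determine 137. With rates of 35% and 20% (mean 27.5%), two-sided, pooled variance under the null:

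n = [1.960·√(2·0.275·0.725) + 0.842·√(0.35·0.65 + 0.20·0.80)]² / 0.15² = (1.238 + 0.524)² / 0.0225 ≈ 137.9, which rounds up to 138.

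The unpooled formula gives 135.2. Other inputs also come close:
- 30% versus 15% with continuity correction: 134.
- One-sided 0.05 with rates near 50%: 134 to 136.
- Non-inferiority with a 15-point margin, both rates 50%, one-sided 0.05: 138.

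All of these are calculations for a crude comparison. I use 35% versus 20% below, as an assumption.

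**Step 2. Crude power.** Power = Φ{[0.15·√137 − 1.238] / 0.622} = Φ(0.832) = 79.7%.

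This depends on the assumed rates. At 137 per arm, two-sided, it is 84.8% for 30% versus 15%, 75.8% for 40% versus 25%, and 71.2% for 50% versus 35%.

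**Step 3. Power with adjustment.** To a good approximation, adjustment divides the effective sample size by (1 − R²), so n_eff = 137 / (1 − R²), and the interval width on the risk-difference scale is multiplied by √(1 − R²). At 35% versus 20%:

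| R² (assumed) | n_eff per arm | Power | n per arm for 80% power | Interval width relative to crude |
|---|---|---|---|---|
| 0 | 137.0 | 79.7% | 138 | 1.00 |
| 0.05 | 144.2 | 81.7% | 132 | 0.97 |
| 0.10 | 152.2 | 83.8% | 125 | 0.95 |
| 0.20 | 171.2 | 87.8% | 111 | 0.89 |
| 0.30 | 195.7 | 91.7% | 97 | 0.84 |

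To give R² a feel: if half the patients had a 10% risk and half a 40% risk, the mean is 25%, the between-group variance is 0.15² = 0.0225, and R² = 0.0225 / (0.25·0.75) = 0.12.

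**Step 4. Is the crude test sound?** A simulation of 4,000 trials of 274 patients used one strong baseline covariate (assumed log odds ratio 1.5 per standard deviation). The adjusted analysis was a linear model with robust standard errors. Type I error was 5.3% crude and 5.4% adjusted. With a true effect in the same setting, power was 77% crude and 87% adjusted. Both tests are valid, and adjustment is the more powerful.

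**Step 5. Chance imbalance.** For a factor present in 30% of patients, the standard error of the difference between arms is √(2·0.3·0.7/137) = 0.0554. The probability of a gap of at least 10 points is 2·[1 − Φ(0.10/0.0554)] = 7.1%. At prevalences of 10%, 20% and 50% it is 0.6%, 3.9% and 9.8%. With risks of 40% and 10%, such a gap moves the event-rate difference by 0.10 × 0.30 = 3 points, against a 15-point target.

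**The case against.** The strongest reply is that covariates are usual content of a statistical analysis plan, that such a plan may exist, and that the protocol never calls its analysis unadjusted. Relative risks can be adjusted and log-rank tests stratified. This stands in part: nothing in the protocol rules out adjustment, and the crude reading is inferred from how the methods are named. It does not dispose of the point, because the protocol is not silent on method. It names one twice, and an adjusted primary analysis introduced later, after some of the planned six-monthly interim looks, could appear data-driven.

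Three stronger readings are tempting, and the documents support none of them.
- A reader might infer that the crude analysis is biased by case-mix imbalance. It is not: randomisation protects the type I error, and chance imbalance is already reflected in the standard error.
- A reader might infer that the trial is underpowered for want of adjustment. If 35% versus 20% is what was planned, the crude test already delivers the stated power, and adjustment is a gain on top.
- A reader might infer that the protocol intends to adjust for bypass or cross-clamp time. It only lists them as data to collect.

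It is also fair that the size of the gain is assumed throughout, that the power figures are for a difference test while the hypothesis is one of non-inferiority, and that an age range of 10 to 18 years may limit what age contributes.

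**Conclusion.** The point holds as a recommendation for a more precise analysis, not as an error or contradiction. The protocol names crude methods for a mixed surgical population while already collecting baseline information that could sharpen the comparison.

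The gain is about 2 power points at R² = 0.05 and about 12 at R² = 0.30, from a base of about 80%. This rests on assumed rates of 35% versus 20%, a two-sided test at 0.05, and an R² that the documents do not supply. The narrowing of the interval, roughly 3% to 16% over the same range, does not depend on the assumed event rates and carries over to a non-inferiority reading.

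**What to change.** Pre-specify the primary comparison of the composite as a covariate-adjusted relative risk with a 95% confidence interval, for example from a logistic model with standardisation over the trial population. Adjust for age and for planned procedure type, grouped into a few categories defined before any outcome data are seen. Keep the crude relative risk as a supportive analysis.

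State that only factors known before randomisation may be adjusters, and that bypass and cross-clamp time are excluded. Procedure type should mean the operation planned at randomisation, not the one finally performed.

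Adjustment for surgeon and stratification of the randomisation by procedure category are optional. The number of surgeons is not given, and stratification would have to be settled before the allocation list is generated.

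The cost is a few sentences in the protocol or analysis plan and agreement on the procedure groups. Age and procedure type fall within the data already listed, but the grouping has to be written and the planned operation captured before randomisation. The main drawback is sparse procedure categories, which need to be merged in advance.
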